## Abstract

**Background:**

Post-stroke cognitive impairment (PSCI) lessens quality of life, restricts the rehabilitation of stroke, and increases the social and economic burden stroke imposes on patients and their families. Therefore effective treatment is of paramount importance. However, the treatment of PSCI is very limited. The primary aim of this protocol is to propose a lower cost and more effective therapy, and to confirm the long-term effectiveness of a therapeutic regimen of Traditional Chinese Medicine (TCM) rehabilitation for PSCI.

**Methods/Design:**

A prospective, multicenter, large sample, randomized controlled trial will be conducted. A total of 416 eligible patients will be recruited from seven inpatient and outpatient stroke rehabilitation units and randomly allocated into a therapeutic regimen of TCM rehabilitation group or cognitive training (CT) control group. The intervention period of both groups will last 12 weeks (30 minutes per day, five days per week). Primary and secondary outcomes will be measured at baseline, 12 weeks (at the end of the intervention), and 36 weeks (after the 24-week follow-up period).

**Discussion:**

This protocol presents an objective design of a multicenter, large sample, randomized controlled trial that aims to put forward a lower cost and more effective therapy, and confirm the long-term effectiveness of a therapeutic regimen of TCM rehabilitation for PSCI through subjective and objective assessments, as well as highlight its economic advantages.

**Trial registration:**

This trial was registered with the Chinese Clinical Trial Registry (identifier: ChiCTR-TRC-14004872) on 23 June 2014.

**Electronic supplementary material:**

The online version of this article (doi:10.1186/s13063-015-0795-x) contains supplementary material, which is available to authorized users.

## Background

Cognitive impairment is considered as one of the major long-term effects after a stroke [1, 2]. In China, post-stroke cognitive impairment (PSCI) occurs in 55.9 % of all patients who suffer a stroke [3]. In the United States, the total annual costs of stroke are thought to increase to US$240.67 billion by 2030, and a large part of these costs is caused by cognitive impairment [4]. In addition to the direct effect on the quality of life of patients and their families [5], there are also indirect effects of this cognitive dysfunction on functional recovery, due to the inability to actively participate in functional training and the failure to follow task instructions [6]. Cognitive impairment can influence patients’ self-confidence and may cause depression, anxiety, and unwillingness to take part in daily activities [7]. The presence of cognitive impairment can also be an important predictor of recovery and has been associated with the risk of recurrent stroke [8]. Therefore, interventions for PSCI are of paramount importance. Unfortunately, the effective interventions of PSCI are very limited [9]. There are some effective drug therapies, such as cholinesterase inhibitors (for example donepezil [10]), cerebral circulation improvement agents, antidepressants, and other investigational drugs; however they have unavoidable side effects, such as anorexia, nausea, vomiting, diarrhea, fatigue, and vertigo [11]. New therapies, such as music therapy [12] and hyperbaric oxygen therapy, have few evidence-based medical studies and more research is needed to determine their safety and efficacy [13].

Cognitive training (CT), which typically involves guided practice on non-specific cognitive activities and specific cognitive functions [14], is used worldwide [15]. There is substantial evidence on the use of CT for cognitive impairment, but systematic reviews suggest that current CT for PSCI still has limited effectiveness [16], and patients cannot improve their cognitive function quickly enough to return to daily life. Therefore, new treatments or comprehensive therapeutic strategies should be of utmost importance in future studies in order to avoid the previously mentioned limitations [17].

Acupuncture is a complementary and alternative therapy. It has a long history in the management of patients with neurological symptoms [18], which has revealed promising cost-effectiveness results [19]. Many studies have highlighted the potential positive effects of acupuncture as a promising treatment for patients with PSCI [20]. Promoting cholinergic neural transmission, facilitating dopaminergic synaptic transmission, enhancing neurotrophin signaling, suppressing oxidative stress, and attenuating apoptosis are some of the proposed mechanisms by which acupuncture improves cognitive function [21]. However, the efficacy of acupuncture is yet to be unequivocally defined. Since the acupoint selection is heterogenous between studies, the conclusions drawn are limited. Thus, the effect of appropriate acupoints needs further research. Only two acupoints, Baihui (DU20) and Shenting (DU24), will be used in this therapeutic protocol, based on our previous study for PSCI treatment [22, 23].

Currently, no single acupuncture intervention has proved to be unequivocally beneficial for PSCI recovery [20]. Systematic reviews have proposed that acupuncture in combination with other therapies can improve cognitive functions significantly [24]. Evidence also suggests that CT combined with other interventions enhances treatment benefits [14] since acupuncture focuses on general cognitive function, while CT addresses one specific impaired cognitive aspect [25]. Their combination, also considered a therapeutic regimen of Traditional Chinese Medicine (TCM) rehabilitation, may prove better at improving cognitive function after stroke. This protocol is sponsored by the 12th Five-year Plan project of the Ministry of Science and Technology of the People’s Republic of China (grant number: 2013BAI10B01).

Further evidence and recommendations for clinical practice supporting a therapeutic regimen of TCM rehabilitation are currently insufficient. Although many studies have addressed the potential use of acupuncture to improve cognitive function, few have explored the effects of a therapeutic regimen of TCM rehabilitation in patients with PSCI [26, 27]. Because of limitations in design or sample size, some of these studies provided equivocal results, thus enhancing the need to conduct high methodological quality trials with large samples and longer follow-up periods. The purpose of this randomized controlled trial is to test the cost-effectiveness of TCM rehabilitation therapy and confirm its effectiveness for PSCI treatment.

## Methods/Design

### Study design

The clinical study is a prospective, multicenter, large sample, randomized controlled trial designed with single-blinded assessments, which is being carried out in seven inpatient and outpatient stroke rehabilitation units. With prior written informed consent, a total of 416 eligible participants will be randomly allocated into the intervention group or control group in a 1:1 ratio. The control group will receive conventional treatment and CT, while, the interventional group will receive conventional treatment and a therapeutic regimen of TCM rehabilitation (CT + acupuncture). A 12-week intervention and 24-week follow-up period will be conducted for this trial. The relative outcomes will be measured at baseline, at the end of intervention (12 weeks), and after the 24-week follow-up period (36 weeks). Fujian University of Traditional Chinese Medicine (FJTCM), as a major undertaker of the study, is responsible for training rehabilitation therapists on standard operation procedure and supervising the progress of this trial in all clinical sites. In addition, the randomization and blinding will be performed by an independent statistician from the Center of Evidence Based Medicine, FJTCM. A flow diagram of this trial is presented in Fig. 1.

**Fig. 1 Fig1:**
[figure not shown]
CONSORT flow diagram of study design

### Participants and recruitment

The participants will be recruited from seven inpatient and outpatient stroke rehabilitation units from FJTCM Subsidiary Rehabilitation Hospital, Guangdong Province Traditional Chinese Medical Hospital, The First Affiliated Hospital of Jinan University, Traditional Chinese Medicine Hospital of Xinjiang Uygur Autonomous Region, The Affiliated Huashan Hospital of Fudan University, Zhongshan Hospital of Traditional Chinese Medicine, and ShiyanTaihe Hospital, all in China. Our study will be advertised on each hospital’s internet homepages. Posters informing patients about this trial are displayed in several community rehabilitation centers and hospitals. Interested patients can contact the project leader (PL) through their therapists, via phone, email, or mail. After obtaining informed consent, the prospective participants are screened according to the inclusion and exclusion criteria. Those who comply with all criteria are eligible to participate. The eligible individuals are invited to participate in the trial and are directed to a diagnostic assessment by a neurologist, followed by rehabilitation assessments. Data on the design of the study is shown in Table 1.

**Table 1 Tab1:** Study design

Items		Before intervention		Intervention period		Follow-up period	
		Screening	Evaluate^a^	Weeks 1-12	Evaluate^b^	Weeks 13-36	Evaluate^c^
Enrollment		×					
Informed consent		×					
Basic information		×					
Inclusion and exclusion criteria		×					
Randomization and allocation		×					
Primary outcomes	MMSE	×	×		×		×
Secondary outcomes	MoCA		×		×		×
	TAP		×		×		
	WMS		×		×		
	TMT		×		×		
	Stroop		×		×		
	MBI		×		×		×
	SF-36		×		×		×
	FMA		×		×		
	*f*MRI		×		×		
	ERP		×		×		
Treatment recorded				×		×	
Adverse events recorded				×		×	
Rehabilitation expenses questionnaire				×		×	×

^a^Evaluation in the week before intervention. ^b^Evaluation in the week after intervention. ^c^Evaluation in the week after follow-up. Abbreviations: MMSE, Mini-Mental State Examination; MoCA, Montreal Cognitive Assessment; TAP, Test of attentional performance; WMS, Wechsler memory scale; TMT, Trail Making Test A and B; Stroop, Stroop Test; MBI, Modified Barthel Index; SF-36, 36-Item Short Form Health Survey; FMA, Fugl-Meyer Motor Assessment; *f*MRI, Functional magnetic resonance imaging; ERP, Event-related potentials

### Inclusion criteria

This trial’s participants should meet all the following criteria: (1) Signed informed consent by the patient or their guardian to participate in this trial; (2) Present stroke diagnosis according to the fourth national academic conference on cerebrovascular disease’s Diagnostic Criteria for All Kinds of Cerebrovascular Disease [28], and confirmed by computed tomography or magnetic resonance imaging; (3) Mini-Mental Status Examination (MMSE) score ≤24; (4) First ever stroke and within one year post-stroke; (5) Aged between 45 to 75 years; and (6) Patient should be conscious, with stable vital signs.

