### Sample size

The sample size calculation is based on the improvement of MMSE scores, which is used as the primary effect indicators to estimate. According to the similar published articles [29], the mean difference in MMSE scores before and after treatment is three points, with a standard deviation of 1.5. According to our pilot study, a therapeutic regimen of TCM rehabilitation (CT + acupuncture) can probably improve the MMSE by 3.52 points on average compared to the control group. Improvement will be measured according to the same size of the estimation formula:1$$ \mathrm{n}=2\left[{\left({u}_{\alpha }+{u}_{\beta}\right)}^2{\sigma}^2\right]/{\delta}^2 $$

With a type I error of 5 % (α = 0.05) and 90 % power (β = 0.10), it is estimated that a sample size of 173 participants per group will be required. Considering a 20 % dropout rate during the study, a minimum of 416 total participants is needed to reach the target 208 participants per group.

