### Outcome measures

In this study, all the primary and secondary outcomes measures will be tested at baseline (−2 to −1 week) and after the intervention period (12 weeks). After follow-up (36 weeks), the cognitive function, quality of life, and ADL outcomes (MMSE, MoCA, SF-36, and MBI) will also be evaluated. All outcome assessments will be independently performed by experienced and blinded assessors. A summary of all the measures in the trial is shown in Table 1.

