### Statistical methods

All data will be analyzed using SAS version 8.2 (SAS institute Inc., Cary, NC, USA) by an independent blinded statistician. A statistical significance level of 0.05 will be used. For statistical description, continuous variables will be presented for each group using the mean ± standard deviation for normal distribution, and median and interquartile range for non-normal distribution. Categorical variables will be presented by using proportions with their standard error. In order to compare the primary and secondary outcomes between groups, measured at baseline, post-intervention and post-follow-up, the t-test or Mann–Whitney U test will be used for continuous variables and the Pearson chi-squared or Fisher’s exact test will be used for categorical variables. Non-parametric tests, Pearson chi-squared test, or Fisher’s exact test will be used for expressing changes in effect sizes of primary and secondary outcomes between groups before and after treatment, and during the follow-up period (at 12 weeks and 24 weeks).

To adjust the confounding influence if necessary, a general linear model or linear regression will be applied for dependent continuous variables, and a logistic regression model for dependent categorical variables. The analysis of the primary outcome will be expressed by using full analysis set with the principle of intention-to treat and the per-protocol set. The analysis of the secondary outcomes will be performed using the per-protocol set. The analysis of AE will be undertaken by using a chi-square test or Fisher’s exact test. Lastly, the economic evaluation will be assessed using cost-effectiveness analysis. Missing data will be imputed by the last observation carried forward rules.

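### Optional gain in precision: enter the screening MMSE as a second pre-treatment covariate, beside baseline MMSE and centre, in the primary comparison

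*Protocol article*

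**What the plan says.** All references are to the protocol article.

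- **Table 1 (Participants and recruitment)** marks MMSE in the screening column, at the pre-intervention evaluation, after the intervention and after follow-up. It is the only outcome marked at screening. Footnote a times the second reading: "Evaluation in the week before intervention". No date or interval is given for the screening reading.
- **Inclusion criteria** use the score for entry: "Mini-Mental Status Examination (MMSE) score ≤24".
- **Outcome measures** name one baseline: "all the primary and secondary outcomes measures will be tested at baseline (−2 to −1 week"). This window does not match footnote a exactly.
- **Sample size** rests on change in the primary outcome: "The sample size calculation is based on the improvement of MMSE scores". The cited change is 3 points with a standard deviation of 1.5: "the mean difference in MMSE scores before and after treatment is three points".
- **Statistical methods** plan a t-test or Mann–Whitney test at each time point ("In order to compare the primary and secondary outcomes between groups, measured at baseline, post-intervention and post-follow-up") and non-parametric, chi-squared or Fisher tests for change ("between groups before and after treatment, and during the follow-up period"). Covariates come in only conditionally: "To adjust the confounding influence if necessary, a general linear model or linear regression will be applied for dependent continuous variables".

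No section says which pre-treatment MMSE is the value from which change is taken, and none gives the screening score an analytic role.

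**The concern.** A single MMSE reading carries measurement error. A change score inherits that error in full, and a model adjusted for one noisy baseline removes only part of the between-patient variation. A second reading on the same scale, taken before treatment, tells the model more about each patient's starting level. Every randomised patient should have one, because eligibility depends on it. Under the analyses described, that information plays no part in the treatment comparison. What is at stake is precision, and so power, for the primary outcome. Validity is not at stake.

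**Working it through.** **Step 1. Reproduce the plan's own figure.** The Sample size formula is n = 2(u_α + u_β)²σ²/δ². With two-sided α = 0.05, power 90%, σ = 1.5 and δ = 3.52 − 3 = 0.52:

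n = 2 × (1.96 + 1.282)² × 2.25 / 0.2704 = 174.9, so 175 per group against the stated 173.

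This is close enough to take δ = 0.52 and σ = 1.5 as working inputs. (The section words 3.52 as the difference from control, which does not give 173. That is a separate matter.) After 20% dropout, 208 × 0.8 = 166 per arm remain. Power = Φ(0.52 / (1.5 × √(2/166)) − 1.96) = Φ(1.198) = 88.5%.

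**Step 2. Model.** The documents give no correlation or reliability for MMSE, so what follows is a range under assumptions. Let the true starting score have variance Vt, each reading an independent error of variance Ve, and true change a variance Vg. Then 2.25 = Vg + 2Ve. Write s = 2Ve/2.25 for the share of change variance that is measurement error.

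- Change from one pre-score: variance Vg + 2Ve = 2.25.
- Change from the mean of two pre-scores: Vg + 1.5Ve, a reduction of s/4 (6% at s = 25%, 12.5% at 50%, 25% at 100%).
- Linear model on one baseline: residual R1 = Vg + Ve + Vt·Ve/(Vt + Ve).
- Linear model on both scores: R2 = Vg + Ve + Vt·(Ve/2)/(Vt + Ve/2).

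**Step 3. Numbers, with an assumed true MMSE SD of 4 (Vt = 16).** Power is Φ(0.52 / √(2R/166) − 1.96).

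| s | Ve | Vg | R1 | R2 | Further cut | Power, one score | Power, both |
|---|---|---|---|---|---|---|---|
| 25% | 0.281 | 1.688 | 2.245 | 2.108 | 6% | 88.5% | 90.4% |
| 50% | 0.563 | 1.125 | 2.231 | 1.964 | 12% | 88.7% | 92.2% |
| 100% | 1.125 | 0 | 2.176 | 1.668 | 23% | 89.5% | 95.6% |

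The last row is an extreme: it requires that all patients have the same true change.

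**Step 4. Allow for selection at 24.** I simulated the same model with the screening score cut off at 24, unselected means of 20 to 24, true SD 3 to 5 and s of 25% to 100%. The further cut in residual variance was 5.4% to 22.8%. The pre-intervention score exceeded the screening score on average by 0.02 to 0.29 points. The gap was largest when the unselected mean was near 24.

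**Step 5. A less favourable set of assumptions.** Take a pre–post correlation r of 0.5 to 0.8 and a screening–baseline correlation r12 from r up to 0.95, with equal variances. The residual variance goes from 1 − r² to 1 − 2r²/(1 + r12). At the plan's SD and δ, n per group goes from 132–158 with one baseline to 117–151 with both, a further fall in residual variance of about 1% (r = 0.5, r12 = 0.95) to 20% (r = r12 = 0.8). With a change SD of 1.5, these r values imply an MMSE SD of 1.5/√(2(1 − r)), which is 1.5 to 2.4 points. Whether the patients vary that little is not in the documents.

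**Step 6. Bias.** Randomization and allocation concealment says that participants learn their allocation after the baseline assessment, and that therapists are notified then. Screening comes earlier. Neither score can depend on knowledge of the arm, and selection at 24 acts alike on both arms.

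**The case against.** The case against is substantial.

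- **Nothing is stated wrongly.** The article leaves the pre-treatment value undefined, and an analysis plan that is not shown may define it. This stands, and it is why the point is optional.
- **The later score is the ordinary baseline.** A reader might infer that a measurement is wasted, or that the plan picks the wrong baseline. The documents support neither: the screening score decides eligibility, and preferring a score that was not itself selected at 24 is defensible.
- **The screening reading may differ in kind.** Data collection and management separates screeners from outcome assessors, and the article does not say who gives the screening MMSE or when. Equal, independent errors are therefore an assumption. This weakens the size of the gain, and it weakens the case for averaging the two scores. It does not undermine a covariate: the model estimates the weight the screening score deserves, and a poor reading receives little.
- **Not every planned test would benefit.** A post-treatment t-test or Mann–Whitney test uses no pre-treatment score. That is so, and it is why the proposal is a model and not a redefined change score.
- **Adjusting for the single baseline may gain as much.** In part of the Step 5 range it does. In the Step 3 and 4 scenarios the second score adds more than the first adjustment.

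**Conclusion.** The point holds as an optional efficiency improvement of low severity. Two pre-treatment MMSE readings are scheduled, the analysis text gives one of them no role, and both can enter the primary comparison without biasing it. The further cut in residual variance over one baseline covariate is about 5% to 23% under error shares of 25% to 100%, with equal and independent errors and a true MMSE SD of 3 to 5. With other correlations it falls to about 1%. In power at 166 per arm and δ = 0.52, that is from almost nothing to about six percentage points, the upper end being an extreme.

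A reader might go further and infer that the planned comparison is biased or underpowered because of this. The documents do not support that: the omission costs at most some precision, and the planned sample size does not rely on the second reading.

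**What to change.** State in the analysis plan that the primary MMSE comparison is a linear model with treatment, centre, the pre-intervention MMSE and the screening MMSE. Keep the pre-intervention score alone as the descriptive baseline and for within-arm change, because the screening score is selected at 24 or below. In the same edit, make the baseline window in Outcome measures agree with footnote a of Table 1.

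The cost is a sentence or two and one extra model parameter, with no added visit or test. The downside is that the screening score may run about 0.02 to 0.3 points low, equally in both arms. This does not touch the between-arm estimate, but it would inflate within-arm gains if the screening score were used to describe them.

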### Exclusion criteria

Criteria for exclusion are as follows: (1) Patients who suffer from brain tumor, brain trauma, brain parasite disease, or other diseases that could cause cognitive impairment; (2) Patients with severe language, vision, and/or auditory impairment, or neuropsychiatric disorder precluding cognitive examination; (3) Patients who suffer from diseases related to cognitive impairment confirmed by anamnesis, doctors, or families, or with history of cognitive drug use before stroke; (4) Beck Depression Scale score >13; (5) Patients with alcohol or drug abuse; (6) Patients with severe illnesses, such as heart, liver, kidney, and endocrine diseases, and hematopoietic system disease; (7) Pregnant woman or breastfeeding women; or (8) Patients who are included in other clinical trials that would affect the evaluation results of this study.

### Sample size

The sample size calculation is based on the improvement of MMSE scores, which is used as the primary effect indicators to estimate. According to the similar published articles [29], the mean difference in MMSE scores before and after treatment is three points, with a standard deviation of 1.5. According to our pilot study, a therapeutic regimen of TCM rehabilitation (CT + acupuncture) can probably improve the MMSE by 3.52 points on average compared to the control group. Improvement will be measured according to the same size of the estimation formula:1$$ \mathrm{n}=2\left[{\left({u}_{\alpha }+{u}_{\beta}\right)}^2{\sigma}^2\right]/{\delta}^2 $$

With a type I error of 5 % (α = 0.05) and 90 % power (β = 0.10), it is estimated that a sample size of 173 participants per group will be required. Considering a 20 % dropout rate during the study, a minimum of 416 total participants is needed to reach the target 208 participants per group.

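### The printed sample-size inputs do not give 173 per group: a 3.52-point difference with SD 1.5 needs about 4, and the difference that 173 implies (about half a point) is not stated

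*Protocol article*

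**What the plan says.** All the material is in the Sample size section of the protocol article.

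- **Quantity used for sizing:** "The sample size calculation is based on the improvement of MMSE scores".
- **From published work:** "the mean difference in MMSE scores before and after treatment is three points, with a standard deviation of 1.5". The section does not say which treatment this change belongs to.
- **From the sponsor's pilot study:** the regimen of CT plus acupuncture "can probably improve the MMSE by 3.52 points on average compared to the control group". No SD is given for the pilot.
- **Formula:** n = 2(u_α + u_β)²σ²/δ², per group.
- **Error rates:** "With a type I error of 5 % (α = 0.05) and 90 % power (β = 0.10"). Sidedness is not stated.
- **Result:** "it is estimated that a sample size of 173 participants per group will be required", raised to 208 per group and 416 in total for 20% dropout.

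The Study design section confirms equal allocation: "randomly allocated into the intervention group or control group in a 1:1 ratio". The article does not say which number was entered as δ.

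**The concern.** As worded, 3.52 is the advantage over control, so it is the natural δ. With an SD of 1.5, that is an effect of more than two standard deviations, which a handful of patients per arm would detect. A requirement of 173 per arm is about 45 times larger than the formula gives (173/3.8).

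This paragraph is the only quantitative justification for enrolling 416 people, and the design difference is the benchmark against which the primary MMSE result will be read. A reader who takes the text at face value sees a trial aimed at a 3.5-point benefit. The printed n, taken with the printed SD, corresponds to a benefit of about half a point on a 30-point questionnaire. The two targets differ by a factor of about 6.8 (3.52/0.52), and the article does not show which one the design rests on.

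**Working it through.** **Inputs** (protocol article, Sample size): σ = 1.5, α = 0.05, power 0.90. Quantiles: u_β = 1.2816; u_α = 1.96 two-sided or 1.6449 one-sided.

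**Numerator of the formula**

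- Two-sided: 2 × (1.96 + 1.2816)² × 1.5² = 2 × 10.508 × 2.25 = 47.29
- One-sided: 2 × (1.6449 + 1.2816)² × 1.5² = 2 × 8.564 × 2.25 = 38.54

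**Step 1. Try to reproduce 173 from the printed figures** (n = numerator/δ²)

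| δ | Where it comes from | n two-sided | n one-sided |
|---|---|---|---|
| 3.52 | stated as difference from control | 47.29/12.39 = 3.8, so 4 | 3.1, so 4 |
| 3.00 | stated before/after change | 47.29/9 = 5.3, so 6 | 4.3, so 5 |
| 0.52 | 3.52 − 3.00, not stated | 47.29/0.2704 = 174.9, so 175 | 142.5, so 143 |

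Neither stated figure comes near 173. Using the t distribution raises the first row only to about 5 to 6 per group. The two-sided 0.52 row comes close. With rounded quantiles (1.96 and 1.28) it gives 174.7, which is still 175 and not 173.

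**Step 2. Solve for the difference that 173 implies at SD 1.5**

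- Two-sided: δ = √(47.29/173) = 0.523
- One-sided: δ = √(38.54/173) = 0.472

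**Step 3. Solve for the SD that would rescue δ = 3.52**

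- Two-sided: σ = √(173 × 3.52²/2)/3.2416 = 32.74/3.2416 = 10.1
- One-sided: 32.74/2.9265 = 11.2

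Both are about seven times the printed 1.5.

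**Step 4. Power with 173 per group if δ = 0.52, SD 1.5, two-sided**

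- Standard error of the difference: 1.5 × √(2/173) = 0.1613
- 0.52/0.1613 − 1.96 = 1.264, so power is about 89.7%

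For δ = 3.52, power with 173 per group is effectively 100%.

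**The case against.** The strongest objection concerns how far the explanation can be taken. The subtraction 3.52 − 3.00 comes so close to 173 that a reader might conclude that 3.52 is the within-group gain on TCM rehabilitation, that 3.00 is the within-group gain on CT, and that the trial is definitely sized for 0.52 points. The article does not support that as fact:

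- It takes the 3 points from published work as a before/after change, and does not link it to CT or to the control arm.
- It describes 3.52 as a comparison with control.
- 0.52 gives 175, which misses the printed figure by 2.

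A reader might also infer that 0.52 is the only difference that can produce 173. That holds only for an SD of 1.5 and a two-sided test. The section does not state sidedness, and one-sided the implied difference is about 0.47. The 1.5 is attached to the published change and not to the pilot.

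A third tempting inference is that the trial is seriously underpowered. It is not on either reading: with 173 analysed per group, power is close to 100% for 3.52 and about 89.7% for 0.52.

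These objections limit the explanation but do not repair the arithmetic. No section supplies another δ or SD that gives 173. Nor is this a detail left to a fuller document, because the article prints the formula, the inputs and the answer, and they conflict.

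**Conclusion.** The point stands in this form: the printed inputs do not yield 173 per group. In the protocol's own formula, 3.52 points with SD 1.5 needs about 4 per group, and 3.0 points about 6. At SD 1.5, 173 per group implies an unstated between-group difference of about 0.52 points two-sided, or 0.47 one-sided. A subtraction of 3.00 from 3.52 is the most plausible source, but it is an inference for the sponsor to confirm.

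The mismatch itself does not depend on that inference or on sidedness. It rests only on the formula, SD, error rates and difference as printed. The figure of about half a point does depend on the SD of 1.5 being the one used.

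**What to change.** The sponsor should first state the δ, SD and sidedness that were actually entered, and then make the description of 3.52 agree with them.

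- **If δ was 0.52:** give the design difference as 0.52 MMSE points with SD 1.5 and two-sided α 0.05. Remove the wording that makes 3.52 a comparison with control. Keep 173 per group and 416 in total, and restate power as about 89.7%. Replacing 173 by 175 instead would, under the article's own 20% addition, give 175 × 1.2 = 210 per group and 420 in total, so keeping 173 with the restated power is the simpler correction.
- **If 3.52 really is the between-group difference:** say that 173 does not come from this calculation and give its actual basis.
- **If other values were used** (for example a one-sided test or a different SD): print them with the resulting n.

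The cost is rewording one paragraph, with no change to enrolment. If 0.52 is confirmed, the stated target effect becomes less impressive.

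### The 20% dropout allowance multiplies 173 per group by 1.2 instead of dividing by 0.8, so 416 is not the minimum that the protocol's own inputs imply

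*Protocol article*

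**What the plan says.** All the figures are in the Sample size section of the protocol article. For a type I error of 5% and a power of 90%, "it is estimated that a sample size of 173 participants per group will be required". The next sentence makes the allowance for losses: "Considering a 20 % dropout rate during the study", it states that "a minimum of 416 total participants is needed to reach the target 208 participants per group".

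The total of 416 is repeated in the Abstract and under Study design. The article does not show how 208 was obtained from 173, and no other section revises either number.

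**The concern.** A dropout rate during a study is a proportion of the people who enter it. To finish with a required number, that number is divided by one minus the rate. Adding the same percentage to the required number always gives too few, because the loss then applies to the larger, inflated group.

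The section gives the required number, the rate and the result together, so a reader will take 416 as the smallest total that still leaves 173 per group, and hence 90% power, after 20% dropout. If the step is wrong, that claim is wrong as printed, whatever the reason for choosing 173.

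**Working it through.** **Inputs, all from the Sample size section:** required number per group 173; dropout 20%; target 208 per group, 416 in total; power 90% at α = 0.05. Allocation is 1:1 (Randomization and allocation concealment).

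**1. Reproducing the printed figure.** 173 × (1 + 0.20) = 207.6, rounded up to 208; 2 × 208 = 416. This matches exactly.

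**2. The number that the stated rate implies.** 173 / (1 − 0.20) = 216.25, rounded up to 217; 2 × 217 = 434. Rounding does not explain the gap: 216 × 0.8 = 172.8, just below 173, and 217 × 0.8 = 173.6. The printed total is 434 − 416 = 18 too low.

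**3. What 208 per group leaves.** 208 × 0.8 = 166.4, about 166 completers per group. Against 173 this is 7 short (6.6 before rounding), about 4%.

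**4. The dropout that 416 can absorb.** 1 − 173/208 = 35/208 = 0.168, or 16.8%.

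Steps 1 to 4 use only 173, 20% and 208. They need no effect size and no standard deviation.

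**5. Effect on power, anchored on the protocol's 173 per group for 90%.** The article's formula is n = 2(u_α + u_β)²σ²/δ². With σ and δ fixed, u_α + u_β is proportional to √n. Assume a two-sided test, since the sidedness is not stated:

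- at 173: 1.960 + 1.282 = 3.242
- at 166: 3.242 × √(166/173) = 3.242 × 0.9796 = 3.175
- 3.175 − 1.960 = 1.215, and Φ(1.215) = 0.888

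Power is therefore about 88.8%, a loss of about 1.2 points. A one-sided 5% test barely changes this: (1.645 + 1.282) × 0.9796 − 1.645 = 1.222, and Φ(1.222) = 0.889.

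**6. Why no effect size is used in step 5.** The section says that the regimen "can probably improve the MMSE by 3.52 points on average compared to the control group" and gives a standard deviation of 1.5. Put literally into the formula, these give 2 × 3.242² × 1.5² / 3.52² = 3.8, so 4 per group, not 173. A difference of 3.52 − 3 = 0.52 gives 174.9, so 175, which is close to 173. But 0.52 is a reader's reconstruction and is not stated in the article.

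**The case against.** **Adding 20% is a common shortcut.** It is, but it does not deliver the required number at the stated rate. The text describes the 20% as dropout during the study and calls 416 a minimum. On that wording the minimum is 434.

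**The primary analysis keeps dropouts.** Under Statistical methods, the primary outcome is analysed in the full analysis set by intention to treat, and missing values are filled by last observation carried forward. Dropouts can therefore stay nominally in that analysis, so 166 should be read as completers and not as everyone analysed. That part stands. It does not rescue the calculation: the Sample size section itself treats dropouts as lost by adding an allowance for them. The primary outcome is also analysed in the per-protocol set, and the secondary outcomes use that set, from which dropouts would normally be missing.

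**Timing.** The 20% covers a 36-week study, while treatment ends at week 12. If some dropouts leave during the 24-week follow-up, more than 166 per group remain at week 12. The article gives no split. The shortfall of 7 per group is therefore an upper bound at week 12 and holds in full at week 36. This stands as a qualification.

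**A stronger reading that the documents do not support.** A reader might infer that power is 88% rather than 90%, using a difference of 0.52 and a standard deviation of 1.5; at 166 per group these give 88.5% by the normal approximation and 88.3% by a t-test. That rests on the unstated 0.52. It also mixes two discrepancies, because at 0.52 even 173 per group gives only 89.7% by the normal approximation. The part due to the dropout step is again 89.7 − 88.5 = 1.2 points.

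**Conclusion.** The point holds as an arithmetic error in a printed sample-size figure. At the protocol's own 20% rate, 208 per group leaves about 166 completers instead of 173, and the stated minimum should be 434 rather than 416. Equivalently, 416 covers about 16.8% dropout. These figures follow from stated numbers alone.

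The consequence is small. In an analysis that loses dropouts, and accepting that 173 per group gives 90%, power is about 88.8%. A reader might infer that the trial is seriously underpowered. The documents do not support that: the loss is about 1.2 points, and the full analysis set nominally retains dropouts.

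The mismatch between the stated 3.52-point effect and 173 per group is a separate issue in the same section. It neither causes nor excuses the dropout step.

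**What to change.** Keep 416 and replace the dropout sentence in the Sample size section with one to this effect: *randomising 416 participants (208 per group) retains 173 per group provided that dropout does not exceed about 16.8%.* This needs no assumed effect size.

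If the 20% rate is to remain in the text, add that it would leave about 166 completers per group and, taking 173 per group as giving 90%, about 88.8% power for analyses that lose dropouts. Do not write in a power figure based on a difference of 0.52. The separate question of which effect size supports 173 should be settled on its own.

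The cost is one sentence, and the stated margin becomes slightly less favourable. Recruitment, conduct and analysis do not change, which suits a trial that has enrolled since July 2014. Keeping both 20% dropout and 173 completers per group would instead mean 434 participants, 18 more; a loss of about 1.2 points gives little reason to require that.
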